### Analyses

The principal analyses will be by intention-to-treat, regardless of the degree of application and adherence to the INDI program guidelines by the patients, professionals, and healthcare centers or areas.

The quantitative analyses of this study will be based on the clinical records of all eligible depressed patients seen in the participating primary care centers. That is, we will work with the entire population and not with a sample, which provides the strengths to minimize selection bias and is based on an independent data collection [36].

At baseline, we will perform a comparative analysis between the areas assigned to the experimental group and the areas of the control group to ensure similarity between the characteristics of their health organizations and clinical practices related to depression.

Analyses of the quantitative variables will consist of both pre-post and intervention-control comparisons of the sets of indicators with quantitative results, with key control points at baseline and at 12 months.

Based on the nature and characteristics of the various questionnaires described in the measures section, the analyses will be carried out in a pre-post comparison framework or as a retrospective analysis at an advanced stage of the implementation process, which we have set at 12 months.

The interviews with focus groups will be recorded and transcribed in their entirety. We will then use a thematic framework analysis to classify and organize the data according to key topics, concepts, and predefined constructs that will be analyzed using qualitative techniques adapted from the normalization process theory [37] to identify barriers and facilitators in the various domains, focusing on ‘hot spots’, for example, dilemmas, conflict situations, and uncertainties.

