### Design

This is a study of the implementation of a healthcare intervention with a quasi-experimental design and mixed measurement methods that include both qualitative techniques and analysis and quantitative indicators.

The design involves defining several geographic areas in which the INDI program will be implemented as well as other comparable areas which will serve as the control, where depression will be treated as usual.

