**Fig. 1 Fig1:**
[figure not shown]
Counties of Catalonia where the study will be carried out. Modified from Martí8888 [CC BY-SA 4.0]. Available at: https://commons.wikimedia.org/wiki/File:Catalonia_base_map_42_comarques.png

The Gerència Territorial Camp de Tarragona is the main primary care provider in the counties of Alt Camp, Conca de Barberà, Baix Camp, el Tarragonès and el Priorat in southeastern Catalonia and manages 20 primary care centers serving an assigned population of 323,740 people. The entity providing mental healthcare services is the Institut Pere Mata, with a community network including three adult mental healthcare centers located in the cities of Reus, Tarragona, and Valls.

The Servei d’Atenció Primària Vallès Occidental Est is the primary care provider for part of the county of Vallès Occidental, located in the Barcelona metropolitan area, and it manages 22 primary care teams serving an assigned population of 386,811 people. The Parc Taulí Corporation is the mental healthcare services provider and has two adult mental healthcare centers located in the city of Sabadell. This entity also manages a primary care center located in Sabadell that is participating in the project.

In each of these two regions, an area for testing the intervention and a comparable control area will be selected. The assignment of an experimental or control condition will not be random, but we will ensure that the areas are comparable in their sociodemographic, health, and organizational characteristics. Because the aim of the study is to test implementation under real conditions and we primarily anticipate using intention-to-treat analyses, exclusion criteria have not been established for centers or professionals as long as they are within the areas defined for this experiment.

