### Intervention (INDI program)

INDI is a multi-component program based on the chronic care model and previous collaborative care programs adapted to the conditions of primary care in the Catalan public healthcare system. It is made up of training, clinical and organizational components, as well as health education for patients. Its objective is to improve clinical management and clinical outcomes in depression. The program focuses on how the approach to depression is managed by the primary care team, and introduces the role of the care manager, enhances the relationship between different levels of care, strengthens the skills of the healthcare professionals involved, and empowers patients. It is based on the optimization of available resources rather than the need for additional resources. The characteristics of this program have been published previously [17, 20].

The INDI model has been tested in a clinical trial in which its clinical efficacy was found to be comparable to that reported in the scientific literature for similar interventions, with an effect size of 0.35 compared to standard treatment and depression response and remission rates 15–20% greater during 12 months of follow-up [17]. In a 3-year analysis, an attenuation of the effect parallel to the decrease in the adherence of professionals to the INDI program was observed, in the absence of an active strategy to promote the sustainability of the program [21].

In addition to clinical effectiveness, economic impact is a considerable factor in the decision to implement a healthcare intervention. The evaluation of this parameter showed an incremental cost-effectiveness ratio of €4056/quality-adjusted life year (QALY) or €4.5/depression-free day. This means that INDI yields better results than standard treatment for a modest increase in cost, which translates into a favorable cost-effectiveness ratio according to commonly accepted criteria in the field of healthcare innovation [22].

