### Control

The centers in the control group will not establish any special treatment practices, but the organization and professionals will offer patients with depression the best care based on standard criteria. As this is a study of implementation under real conditions the centers in the control group will not be prevented from accessing or applying any other initiative for training or healthcare quality improvement that exists in the study period.

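### With non-randomly assigned areas, the plan names pre-post and intervention-control comparisons but not the between-area difference in change as the effect of INDI

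*Protocol article*

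**What the plan says.** The Design section of the protocol article describes a "quasi-experimental design and mixed measurement methods that include both qualitative techniques and analysis and quantitative indicators", with INDI areas and comparable usual-care areas. Under Settings and participants, one test area and one control area are to be chosen in each of two regions: "The assignment of an experimental or control condition will not be random, but we will ensure that the areas are comparable" in sociodemographic, health and organizational terms.

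The Analyses section then fixes the contrasts: "Analyses of the quantitative variables will consist of both pre-post and intervention-control comparisons of the sets of indicators with quantitative results". It sets baseline and 12 months as the main time points for them. It also plans a baseline comparison of the INDI and control areas "to ensure similarity between the characteristics of their health organizations and clinical practices related to depression". It states no consequence for the effect estimate if the areas turn out to differ.

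The Control section adds that control centers "will not be prevented from accessing or applying any other initiative for training or healthcare quality improvement that exists in the study period".

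The article does not mention a difference in change, an area-by-period term or a baseline-adjusted contrast. It does not exclude one either.

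**The concern.** In a non-randomized comparison of a few areas, each of the two named contrasts has its own source of bias. The change over time within the INDI areas picks up anything else that altered depression care over the same period. The difference between areas at 12 months picks up whatever differed between them at the start. With one test and one control area per region, such differences cannot be expected to average out.

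Two statements in the article may reassure a reader more than they should. A baseline comparison shows whether areas look alike on what was measured; it does not make them alike. The Analyses section also presents the use of all eligible patients as a protection against selection bias. Complete capture of patients does not remove confounding by area, and it makes a biased contrast more precise.

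If the two contrasts disagree on an indicator, the section does not say which one answers the question. Table 2 lists many indicators, and the results feed a proposal to extend INDI across the Catalan system. The contrast that defines the effect should therefore be settled before the data are seen.

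**Working it through.** The article states no sample size, significance level or power, so there is no figure of the plan to reproduce. The check is algebra on the four cell means, followed by an illustration with assumed values.

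**Inputs from the protocol article**
- Areas assigned non-randomly (Settings and participants).
- Pre-post and intervention-control contrasts, with baseline and 12 months as the key points (Analyses).
- Earlier INDI trial: "depression response and remission rates 15–20% greater during 12 months of follow-up" (Intervention, INDI program). This is used only to scale the illustration, read as 0.15 to 0.20 on the proportion scale.

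**Assumed inputs, not in the documents**
- Control baseline proportion 0.40.
- Common trend t from 0 to 0.10.
- Baseline gap g (INDI minus control) from -0.05 to +0.05.
- 200, 500 or 1000 patients per cell.

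**Algebra.** Let e be the true effect and p the control baseline.
- Control: p at baseline, p + t at 12 months.
- INDI: p + g at baseline, p + g + t + e at 12 months.
- Pre-post in INDI areas: (p + g + t + e) - (p + g) = e + t.
- INDI minus control at 12 months: (p + g + t + e) - (p + t) = e + g.
- Difference in change: (e + t) - t = e.

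**Results over the assumed ranges**

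| True e | Pre-post, e + t | 12-month contrast, e + g | Difference in change |
|---|---|---|---|
| 0 | 0 to 0.10 | -0.05 to 0.05 | 0 |
| 0.15 | 0.15 to 0.25 | 0.10 to 0.20 | 0.15 |
| 0.20 | 0.20 to 0.30 | 0.15 to 0.25 | 0.20 |

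**Chance of a false positive when e = 0.** Suppose a trend or a gap of 0.05 makes the affected contrast 0.40 versus 0.45. With n per cell, SE = sqrt[(0.40 x 0.60 + 0.45 x 0.55)/n] = sqrt(0.4875/n). At n = 500, SE = 0.0312, z = 0.05/0.0312 = 1.60, and the chance of two-sided significance at 0.05 is about Phi(1.60 - 1.96) = 0.36. At n = 200 it is about 0.17 and at n = 1000 about 0.62. These figures ignore clustering by center, so they show only how the risk grows with n.

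**Limit of the better contrast.** Let the trend be tI in INDI areas and tC in control areas. The difference in change is then e + (tI - tC), which equals e only if trends are parallel. If other initiatives raised the control trend alone by 0.05, it would read e - 0.05. The pre-post change in the INDI areas, e + tI, would not move.

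**Precision.** With four independent cells of equal size and variance v/n each, a simple contrast has variance 2v/n and the difference in change 4v/n. Its standard error is therefore sqrt(2) = 1.41 times as large. Correlation within centers over time would alter this ratio.

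**The case against.** The strongest defence is that two groups measured before and after make a controlled before-after design, and that the sentence in the Analyses section is an ordinary short description of one. The article is condensed, the analysis plan is not shown, and model terms, covariates and clustering are commonly left to it. This stands in part: the text is compatible with a difference-in-differences analysis, and missing model detail is not a fault here. But the sentence goes beyond silence. It states what the quantitative analyses will consist of, and the contrast that the design most needs is not among them.

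Several stronger readings are tempting, and the documents do not support them:
- *That the two comparisons replace the interaction, or that neither can estimate the effect.* Nothing says they are run in isolation. By the algebra, pre-post is unbiased if t = 0 and the 12-month contrast is unbiased if g = 0. The plan does aim to choose comparable areas.
- *That other initiatives in control centers bias the INDI pre-post change.* The Control section concerns control centers only. Differential uptake there would threaten parallel trends, and with them the recommended contrast.
- *That only two time points will be used.* Baseline and 12 months are called key points, and response and remission are also set at 6 months.
- *That a long pre-2018 series is available for every outcome.* The article says the indicators come from a primary care records database. It does not establish earlier recording of PHQ-9, GAF or MINI.

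It is also fair to say that implementation success rests on acceptability, penetration and sustainability as well as on these indicators, so the decision to generalize does not hang on one estimate.

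**Conclusion.** The concern holds in a limited form. The Analyses section names two families of comparison, each open to a bias that non-random assignment of areas allows, and does not name the contrast that removes both fixed area differences and common trends. The baseline comparison does not close the gap.

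The bias equals the trend in one contrast and the baseline gap in the other. Its actual size is unknown, because the article gives neither quantity; the 0.05 and 0.10 values are illustrative. The advantage of the difference in change rests on parallel trends, which one pre-period and one post-period cannot test. The point is the choice of a better main contrast from data already planned. It does not show that the stated analyses are invalid.

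**What to change.** State in the Analyses section or the analysis plan that, for each indicator measurable in both periods and both arms, the main effect is the area-by-period interaction (difference-in-differences). The analysis should account for center and region and adjust for patient case-mix. Report simple pre-post and between-arm differences as descriptive. Describe the baseline comparison as a description of similarity.

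Where the database holds earlier records for an indicator, most plausibly prescribing, diagnosis and visit indicators, use several pre-2018 periods to examine parallel trends. Treat this as optional for PHQ-9, GAF and MINI outcomes. Record which other quality initiatives the control centers take up, so that a departure from parallel trends can be interpreted.

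Cost: mainly wording, since baseline and 12-month data are planned for both arms and the Trial status section reports that pre-intervention data are already being collected. Earlier periods would need a longer retrospective extraction where records exist. The price is a larger standard error than a simple contrast has in the independent-cell case, and reliance on parallel trends.

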## Trial status and forecast execution dates

This study was registered on September 12th, 2017 in *ClinicalTrials.gov* with the *Identifier: NCT03285659* (https://clinicaltrials.gov/show/NCT03285659). Design and preparation of the implementation strategy: June–December 2017; start of implementation: January 2018; implementation procedures: January 2018–June 2019; analysis of the experience, diffusion and publication of the results, design of a proposal for the generalization of the model in primary care centers in the Catalan public health system: June 2019–December 2019.

According the schedule of the trial, we are currently designing and preparing the implementation strategy and collecting pre-intervention data. Procedures for the implementation of the INDI program will be initiated in the selected healthcare regions and primary care centers in 2018.

## Discussion

Depression is a highly prevalent health problem, and has a substantial impact on individuals and society in terms of morbidity and financial cost [2]. It is the mental health disorder most closely associated with suicide [38]. Its clinical management is rooted mainly in primary care, where depression is an everyday problem, and it is also the most frequent reason for referral and shared care between primary care and psychiatry.

This project is an example of translational research: It seeks to bridge the gap between scientific knowledge and clinical practice in the management of depression, a gap that compromises clinical outcomes. The INDI model is an innovative intervention that has been shown in a clinical trial to improve the results of depression management when compared with standard management practices [20, 22]. The challenge is to translate and generalize this apparently useful and effective model, supported by scientific evidence, to healthcare practice under the real-life conditions of primary care.

This proposal has been developed in keeping with the PARIHS framework [27] which constitutes both a consistent theoretical framework and a useful operational structure for establishing and carrying out the implementation strategy, providing the whole project with scientific and methodological integrity.

However, it is important to recognize the limitations of this project. First, the effect size of the INDI model – and collaborative care models in general – in improving the clinical outcomes of depression is small to moderate. Nevertheless, considering the prevalence and burden of disease that depression represents in society, and in primary care in particular, even this moderate effect could translate into significant benefits not only for individuals with depression, but also for the healthcare system and for society as a whole [15]. Second, it has been established that without measures to maintain the involvement of the professionals and the activities of the INDI program, its performance and its beneficial effects decrease over time [21]. For this reason, our implementation strategy should be seen not as an isolated intervention for initiating the program but as a continuous process. Third, the INDI model is intended exclusively for the management of major depression, although it is commonplace in everyday practice to encounter patients with poorly defined depressive states that do not meet the diagnostic criteria or situations of comorbidity of depression with other common mental disorders [39] – particularly anxiety disorders – or chronic physical illnesses [40, 41]. Further research will be needed to refine and expand the range of objectives of the INDI model and adapt it to the management of instances of complexity and comorbidity.

We anticipate that with this implementation experiment we will see substantial changes in the care process for depression in primary care. Further, we expect the implementation and generalization of the program will have a global impact, which may be highly relevant considering the presence and repercussions of depression on society and its association with suicidal behaviors.

## Abbreviations

ARCHO: Assessment of Readiness for Chronicity in Health Care Organizations (in Spanish: IEMAC, Instrumento de Evaluación de Modelos de Atención ante la Cronicidad)
CPCQ: Change Process Capability Questionnaire
DSM-V: Diagnostic and Statistical Manual of Mental Disorders, fifth edition
eCAP: Primary Care Clinical Station (in Catalan: Estació Clínica d’Atenció Primària, i. e., the computerized platform of primary care clinical records)
GAF: Global Assessment of Functioning
ICS: Catalan Health Institute (in Catalan: Institut Català de la Salut)
IDIAP: Primary Care Research Institute (in Catalan: Institut d’Investigació en Atenció Primària)
IEXPAC: Chronic Patient Experience Evaluation Tool (in Spanish: Instrumento de Evaluación de la Experiencia del Paciente Crónico)
INDI: Interventions for Depression Improvement
INNÒBICS: Open Research at the Catalan Health Institute (in Catalan: Innovació Oberta a l’ICS)
MINI: Mini International Neuropsychiatric Interview
PACIC: Patient Assessment of Care for Chronic Conditions
PARIHS: Promoting Action on Research Implementation in Health Services
PERIS: Strategic Plan for Research and Innovation in Health (in Catalan: Pla Estratègic de Recerca i Innovació en Salut)
PHQ-9: Patient Health Questionnaire, 9 items
QALY: Quality Adjusted Life Year
